### Aim and hypotheses

The ORCHIDS study is a genetically informed randomized controlled trial to examine possible G × E and G × G × E (i.e., polygenetic) interactions in the development of child behavior. The study examines parenting in its full scope, from both harsh and inconsistent to positive, sensitive, and appropriate parenting behavior as well as from children’s problem behavior and difficulties to their skills, competencies, and strengths. The primary aim is to investigate whether enrichment of the environment, based on the Incredible Years (IY) parent training, has more effect on a genetically susceptible subgroup of children, and to investigate why this may be the case. We expect that the parent training will bring about an environmental enrichment, leading to behavior changes in the participating parents. Two hypotheses will be tested. First, we expect differential susceptibility, which means that children in the intervention condition who carry one or more susceptibility genes (i.e., carrying a MAOA low activity (short) allele; DAT 10-repeat allele; DRD4 7-repeat allele; DRD2 A1 allele; 5-HTTLPR short allele; and or a COMT val allele) will show a significantly higher decrease of problem behavior and increase of prosocial behavior after their parent(s) received the parent training, compared to children without such susceptibility genes and children in the control group. In the control group, we expect this same genetic subgroup to show most behavior problems and least prosocial behavior. Second, we expect that emotional synchronization in parent–child interactions will mediate the intervention effect. Specifically, we expect that children who carry one or more susceptibility genes show a higher synchronization to their parents’ affect than children without these susceptibility genes. Therefore, we expect these children to benefit most from the increase in parental positive affect and sensitivity induced by the Incredible Years intervention.

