## Methods/Design

### Design

The ORCHIDS study is a randomized controlled trial with an intervention (i.e., the Incredible Years parent training) and a control condition that tests gene-based differential susceptibility to changes in parenting. Participants will be 480 families, with children aged 4–8 who show mild to (sub)clinical externalizing behavior problems. Of those families, 160 will be randomly assigned to the intervention condition and 320 families to the control condition. After enrollment in the trial and randomization, the baseline assessment (pretest) will be carried out. The Incredible Years (IY) program will be implemented after these baseline assessments. Participants in the control condition will receive no intervention, but are allowed –and, in case needed, are assisted– to seek mental health care and parenting support through regular services. Posttest and follow-up assessments will be conducted after 6 months and after 10 months, respectively. Approval for data collection was obtained from the central committee on research involving human subjects in The Netherlands (METC UMC Utrecht, protocol number 11-320/K).

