### Sample size calculation

Power analyses are essential to maximize chances to find significant G × E interactions
[32]. For this calculation, we used a Fixed Effects ANOVA Power Analysis in PASS11
[33]. Based on a meta-analysis that demonstrated a small effect size (*d)* of .20 of the IY intervention
[34], and assuming a small G x E interaction effect and no main effects of genes
[3,35,36], a sample size of *N* = 480 families will be required for investigating our hypotheses in a two-sided test at α = .05 and power (1-β) = .80.

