### Analyses

First, using independent *t*-tests, we will examine whether randomization was successful, comparing baseline levels of externalizing and prosocial behavior across the intervention and control condition. Possible significant differences at baseline will be used as covariates in analyses
[44]. Second, as the longitudinal data of individuals will be nested in families, multilevel latent growth curve analyses in Mplus
[45] will be performed. In this analysis, we will test the interaction between the variables ‘group’ (i.e., intervention vs. control) and ‘genotype’ (i.e., susceptible genotype vs. non-susceptible genotype) to examine possible G × E interactions. In addition, we will take into account families’ ethnic background (i.e., Caucasian vs. non-Caucasian) and additional parental support or (mental) health care families received during the study (i.e., additional self sought care vs. no additional self sought care). Ethnic background and additional care will both be used as covariates in the analyses.

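### The planned group × genotype model cannot tell greater genetic sensitivity from greater starting severity; a second model with group × pretest score would help separate the two

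*Protocol article*

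**What the plan says.** All of this is in the protocol article.

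- **Analyses.** The central test is a product term in a multilevel latent growth curve model: "we will test the interaction between the variables ‘group’ (i.e., intervention vs. control) and ‘genotype", the latter coded as susceptible or not.
- **Analyses, baseline rule.** The check consists of "comparing baseline levels of externalizing and prosocial behavior across the intervention and control condition". Its consequence is that "Possible significant differences at baseline will be used as covariates in analyses". No comparison by genotype is described.
- **Analyses, other terms.** "Ethnic background and additional care will both be used as covariates in the analyses". No product of group with pretest score is named.
- **Aim and hypotheses.** Carriers are expected to gain most from training. The article adds: "In the control group, we expect this same genetic subgroup to show most behavior problems and least prosocial behavior". No time point is attached to that sentence. The primary aim also includes finding out why carriers would benefit more.
- **Design.** "The Incredible Years (IY) program will be implemented after these baseline assessments", so no family has been trained at pretest.
- **Sample size calculation.** The 480 families rest on a training effect "of .20 of the IY intervention", "assuming a small G x E interaction effect and no main effects of genes".

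**The concern.** Randomisation makes the training independent of genotype. It does not make pretest severity independent of genotype. The group × genotype term therefore also picks up moderation by anything that differs between carriers and non-carriers before training, and severity is the obvious candidate. If untrained carriers have the most problems, they may already do so at pretest. If more severe children also gain more from parent training, carriers will show the larger decrease even when, at equal severity, they are no more responsive than other children.

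The two explanations have different consequences. The Discussion argues for tailoring parent training to individual differences in reactivity, for example to praise. If severity is the moderator, the same result could be obtained from an ECBI score without genotyping. The Background offers randomisation as the answer to alternative explanations of gene-environment interactions, but it does not answer this one.

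**Working it through.** **The plan's own figure.** The 480 families cannot be reproduced from the stated inputs. A two-arm comparison with d = .20, two-sided α = .05 and 160:320 has 54% power. A 1-df interaction reaches 80% power at N = 480 when f = .128, but the article calls the interaction only small. That is a separate matter; 480 and 160:320 are used below as given.

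**Inputs from the article.** N = 480, allocation 160:320, training effect .20 SD, two-sided α = .05.

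**Assumed inputs (not in the article).** δ = carrier minus non-carrier difference in pretest severity, .2 to .5 SD. γ = extra training effect per SD of severity, .2 to .3. Carriers 50%, pre-post correlation .6.

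**Formula.** Let the training effect on problems be −(.20 + γ × severity), with no effect of genotype at a given severity. The mean training effect then differs between carriers and non-carriers by −γδ, and the group × genotype term estimates exactly that. If δ = 0 or γ = 0, it is zero.

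**Simulation, 3000 runs per setting, pretest as a main effect only:**

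| δ | γ | −γδ | Mean group × genotype estimate | Rejection at nominal 5% |
|---|---|---|---|---|
| .2 | .2 | −.04 | −.042 | 6.1% |
| .2 | .3 | −.06 | −.063 | 7.2% |
| .3 | .3 | −.09 | −.088 | 9.3% |
| .5 | .3 | −.15 | −.153 | 17.8% |

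A repeat with another seed gave rejection of about 6%, 7%, 9% and 16%.

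**With group × pretest added.** The estimate is within .006 of zero and rejection is 4.3% to 5.6%. The standard error is .156 to .160, against .155 to .158 without the term, so at most about 3% larger (.160/.155 = 1.03).

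**Check on the standard error.** √[(1/160 + 1/320) × (1/.5 + 1/.5)] = .194. Multiplying by √(1 − .6²) = .8 gives .155, which agrees.

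**Other assumptions.** With 30% carriers and correlation .7, both a change-score model and a model with pretest as a main effect carried the same bias. For example, δ = .5 and γ = .2 gave −.098 and −.097, with rejection of 10.7% and 10.0%. Adding group × pretest gave .003 and 4.8%. So the covariate rule would not remove the bias even when triggered. Taking γ up to .4 widens the range to about −.20 SD and 25%.

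**Scale.** Without pretest adjustment, the interaction detectable with 80% power at 160:320 is 2.80 × .194 = .54 SD for 50% carriers and .68 SD for 20% carriers. At .04 to .15 SD, the severity component would usually not reach significance by itself.

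**The case against.** **The test answers the question asked.** The Outcomes and Conclusion sections ask whether genotype moderates the training effect. If carriers start worse and worse children gain more, training really is more effective in carriers. A reader might infer that the planned test is invalid or has an inflated type I error. For total moderation by genotype that is not so. The 6% to 18% applies only to the narrower null of no moderation at a given severity. This objection stands and limits the point to interpretation.

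**Both drivers are assumed.** Nothing in the article says that training works better in more severe children or gives a carrier gap at pretest. Entry at or above the 75th ECBI percentile narrows the range of severity. This stands too. A reader might infer that a severity effect would be reported as genetic susceptibility; the documents support only that it could be.

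**No contradiction about gene main effects.** A reader might infer that expecting untrained carriers to be worst conflicts with the sizing assumption of no gene main effects. Under a crossover the two are compatible: a carrier gap of +a in controls and −a in the trained arm averages (a − a)/2 = 0. The expectation names the control group, not pretest, so applying it to pretest is a reasonable inference but not a statement in the article. The sizing assumption need not be removed.

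**The full plan is not shown, and the model was simplified.** A severity analysis may exist in the fuller plan. The article does, however, state the interaction, the covariates and the baseline rule, and that rule looks only at arms. The simulation used pretest and one later score, not a three-occasion latent growth model. The mechanism should carry over, because an ordinary intercept-slope covariance does not let the group effect on slope depend on the intercept. The exact percentages may differ.

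**Conclusion.** The point holds as a limit on interpretation that is cheap to address. As described, the model lets the training effect vary with genotype but not with starting severity, and the baseline check cannot reveal a severity gap between genotypes. If carriers start .2 to .5 SD worse and the training effect grows by .2 to .3 SD per SD of severity, about .04 to .15 SD of a group × genotype effect would be due to severity, against a planned training effect of .20 SD. Both ranges are assumptions, and the component vanishes if either quantity is zero. The planned test of total moderation stands. What the plan as described cannot support is the further step from carriers gaining more to carriers being more sensitive, which matters for the aim of explaining why they gain more and for the tailoring argument.

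**What to change.** 1. Keep the planned group × genotype model as primary.
2. Report pretest ECBI and MESSY by genotype.
3. Prespecify a second model that adds group × centred pretest score (ECBI or MESSY, matching the outcome) or, within the growth model, group × latent intercept.
4. Present both estimates side by side with intervals, and word the susceptibility and tailoring conclusions by whether the effect persists in the second model.
5. State whether the expectation about carriers in the control group refers to pretest or to later assessments.

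The cost is one extra model on measures already in Table 1, with at most about 3% on the standard error in the simulated settings. There are two downsides. If severity is the route by which genotype acts, the adjusted estimate is a direct effect and is conservative, which is why both should be shown. Measurement error in the pretest also leaves part of the bias: with an assumed reliability of .8, about 1 − .8 = 20%, or .2 × .153 = .03 SD in the largest setting above.

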### Outcomes

Primary outcomes are the possible moderating effects of child genotype on the IY intervention effect (i.e., on the decrease in externalizing problems behavior and/or increase in prosocial behavior of the child). The intervention effect will be assessed with the ECBI, the Matson Evaluation of Social Skills with Youngsters (MESSY
[41]), and the Dyadic Parent–child Interaction Coding System-Revised (DPICS-R
[42,43]), see measures in Table
1. Secondary outcomes will be the observed (changes in) emotional synchronization in parent–child interactions as possible underlying behavioral mechanism to the G × (G) × E interactions.

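### The group × genotype model adjusts for care that families seek after randomisation, so it no longer estimates the randomised effect of the parent training or its moderation by genotype

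*Protocol article*

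**What the plan says.** The primary question is moderation: "Primary outcomes are the possible moderating effects of child genotype on the IY intervention effect" (Outcomes). The Analyses section tests it with multilevel latent growth curves, in which "we will test the interaction between the variables ‘group’ (i.e., intervention vs. control) and ‘genotype" is the term of interest. The same section then takes into account "additional parental support or (mental) health care families received during the study (i.e., additional self sought care vs. no additional self sought care" and concludes: "Ethnic background and additional care will both be used as covariates in the analyses". It does not confine this to a sensitivity analysis, and it describes no model without the care variable.

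On timing, the Design section says: "After enrollment in the trial and randomization, the baseline assessment (pretest) will be carried out". Care during the study therefore follows allocation. On access, the same section says "Participants in the control condition will receive no intervention", but that these families are allowed, and helped where needed, "to seek mental health care and parenting support through regular services". It makes no matching statement for the IY arm and does not bar IY families from such care. No uptake figure is given for either arm.

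**The concern.** A baseline covariate such as ethnic background cannot be changed by allocation. Care sought during the trial can. If uptake depends on arm and also on the child's course, families with the same care status in the two arms are no longer comparable. An IY family that still seeks help may differ in prognosis from a control family that seeks help.

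This matters particularly here. The Background faults earlier correlational work because children may evoke and select their environments, and it offers random allocation as the remedy. Self-sought care is an environment that families select, plausibly in response to the child. If susceptible children respond more to IY, as the first hypothesis states, their families may seek less care, and the covariate then takes up part of the interaction that the trial was set up to detect.

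**Working it through.** **Inputs from the article.** Allocation: "160 will be randomly assigned to the intervention condition and 320 families to the control condition", a 1:2 ratio (Design). Assumed IY effect: d = .20 (Sample size calculation). The article states no figure for the effect of this adjustment, so there is nothing to reproduce. Uptake, reasons for seeking care and the effect of care are not given, and all are assumed below.

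**Why the coefficient moves.** In a linear model with arm and care, least squares gives an exact identity:

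unadjusted effect − adjusted effect = c × (uptake in IY − uptake in control),

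where c is the coefficient of care in the adjusted model. It combines any true effect of care with the selection of families who seek it. The shift is zero only if uptake is equal in the two arms or c is zero, and its direction depends on the sign of c. For the interaction, the corresponding shift is c times the difference between genotypes in the arm difference in uptake.

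**Simulation 1 (no pretest).** 2,000,000 families per scenario, 1:2 allocation, genotype frequency 0.5, lower score better. Problem level during the trial: M = 0.7U + (arm effect, by genotype) × Z, where Z is arm. Care follows a logistic model with intercept −0.85, slope 1 or 0 on M, and an arm shift of −1 or 0. Outcome: Y = M + (care effect) × care + noise.

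| Scenario (assumed) | Uptake IY / control | IY effect, unadjusted → adjusted | G × E, unadjusted → adjusted |
|---|---|---|---|
| A. Care follows problems, no care effect | 13.3% / 31.7% | −0.200 → −0.116 | −0.202 → −0.192 |
| B. As A, care effect −0.2 | 13.3% / 31.7% | −0.168 → −0.121 | −0.194 → −0.188 |
| C. Care unrelated to problems, care effect −0.3 | 13.6% / 30.0% | −0.152 → −0.201 | −0.199 → −0.199 |
| D. As A, but no IY effect and no G × E | 15.5% / 31.7% | −0.001 → +0.072 | 0.001 → 0.001 |
| E. As A, but arm affects uptake only through improvement | 28.0% / 31.6% | −0.199 → −0.183 | −0.203 → −0.186 |
| F. Uptake independent of arm and problems, care effect −0.2 | 29.9% / 29.9% | −0.199 → −0.199 | −0.196 → −0.196 |

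Check with the identity:
- A: (−0.200 + 0.116) / (0.133 − 0.317) = −0.084 / −0.184 = 0.46. Families with care look worse, so adjustment pulls the effect towards zero.
- C: (−0.152 + 0.201) / (0.136 − 0.300) = 0.049 / −0.164 = −0.30. This is the assumed care effect, and adjustment moves the estimate away from zero.

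The largest interaction loss in the table is in E: (0.203 − 0.186) / 0.203 = 8%.

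**Simulation 2 (adding a pretest).** True IY effect −0.20, care without effect. The propensity to seek care correlates .6 with the child's underlying course, and the outcome correlates .3, .5 or .7 with that course.
- Without a pretest, at 40% control and 15% IY uptake, the adjusted effect is −0.12, −0.08 or −0.03.
- With the pretest as a covariate, it is about −0.10 to −0.13 at 40%/15%. The range reaches −0.16 when 30%/15% is included.
- With change from pretest as outcome, and care tracking only stable severity, it is −0.20, so there is no bias.
- With no true interaction, the adjusted G × E term stays near zero.

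**Interaction when care follows problem level.** A true 0.40 SD interaction falls to between 0.37 and 0.31 SD, a loss of up to 0.09 / 0.40 = 23%. Repeat runs put the loss at roughly 6 to 25%. For scale, with an assumed 50% genotype split and one cross-sectional measure, the standard error of the interaction is √[(1/160 + 1/320) × (1/0.5 + 1/0.5)] = √0.0375 = 0.19 SD. The largest loss of 0.09 SD is about half of that.

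**The case against.** The best defence is that adjustment separates the effect of IY from other help that families obtain. That is a legitimate question, but it concerns a different quantity: an effect of IY apart from care. It requires that no unmeasured factor drives both care-seeking and outcome, and a yes/no care indicator cannot secure this.

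Several limits on the criticism stand.
- A reader might infer that uptake differs between arms by design. The article does not say so: it opens care to controls without barring it to IY families, and the covariate is defined for families generally.
- A reader might infer bias towards zero. Scenario C moves the other way, and scenario F shows none.
- A reader might take the fall from −0.20 to −0.03 as the expected damage. That figure concerns the IY main effect, not the primary moderation question, and comes from a model without the pretest that the trial collects.
- The article does not say whether care enters as a time-varying predictor, on the slope or on the outcome. That can be left to an analysis plan not shown here, and the size of any bias depends on it.

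None of this supports keeping the variable in the primary model. Its bias is unknown in size and sign and cannot be judged from the adjusted result alone.

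**Conclusion.** The point holds as a stated choice of covariate that should be corrected before analysis. The article commits to conditioning the main model on a post-randomisation variable that is plausibly affected by arm and by the child's course. The resulting coefficients do not estimate the total randomised effect of IY or its moderation by genotype.

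The size rests wholly on assumed uptake and assumed reasons for seeking care. For the IY effect, the shift may go in either direction, illustratively up to about 0.1 SD against d = .20 when a pretest is used. It is nil if care tracks only stable severity and change is analysed. For the primary G × E test, the expected harm is modest: attenuation of roughly 0 to 25% of a true interaction. The stronger inference, that the covariate would manufacture a G × E finding or invalidate the trial, is not supported. Genotype and allocation remain independent, and the interaction term stayed near zero in the scenarios without a true interaction. This is a should-fix point.

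**What to change.** Remove additional self-sought care from the covariates of the primary model and keep only variables fixed before allocation or measured at baseline. The primary contrast is then between the arms as randomised, with whatever outside care families in each arm use. Report care use by arm and by genotype as a descriptive result. If its influence is of interest, present a care-adjusted or mediation model as a labelled sensitivity analysis with its assumptions stated. The cost is one sentence in the Analyses section, and no new data are needed.

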### Recruitment

In a first screening (see Figure
1), roughly 17.000 families will be targeted through community records via two Dutch regional health care organizations (estimated response rate is 52%, see
[30]). All families will receive a personalized information letter, including the Eyberg Child Behavior Inventory (i.e., ECBI) to screen for children’s problem behavior
[30]. The criterion for inclusion will be a score at or above the 75^th^ percentile. This cut-off is chosen so that at-risk families will be selected, without excluding children and parents with subclinical or even normal-range functioning. Based on a conservative estimation, 889 families (10%) are expected to be eligible for inclusion. Additionally, a second screening will take place to check for exclusion criteria: mental retardation of the parent and/or child (IQ ≤ 70) and not mastering the Dutch language. Based on estimates from similar procedures followed in previous research
[31], 480 eligible families are expected to eventually participate in the ORCHIDS study. These families will receive a second invitation letter and will be contacted for trial participation.

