## Discussion

The ORCHIDS study described in this protocol is a genetically informed randomized controlled trial targeting families with children aged 4–8 who show mild to (sub)clinical behavior problems. The primary aim of ORCHIDS is to assess possible G × (G×)E interactions in the development of child behavior in its full scope – that is, from children’s problem behavior to their competencies. Our large scale randomized controlled trial is one of the first experimental studies of G × E interactions in social development. Experimental manipulation of the environment is crucial in understanding G × E interactions, because it is the only way to prevent confounding gene-environment covariation.

Additional to a single gene approach, we will investigate possible cumulative effects of multiple candidate genes (i.e., G × G × E or polygenetic interactions
[46]). Also, we will make a first attempt to obtain more insight into the behavioral mechanism underlying these G × E interactions by examining (changes in) emotional synchronization in observed parent–child interactions.

Better insight into individual differences in, for example, reactivity to positive parenting behavior like praise, associated with dopaminergic and serotonergic functioning, may help improve the tailoring of behavioral parent training. This seems necessary as the mean effect size of these interventions is modest (Cohen’s *d* = 0.47
[47]). Individualization of use of rewards and praise may help increase the efficiency of these parenting skills. For example, if the emotional significance of the positive message of praise is less well processed, associated with altered dopaminergic functioning, both verbal and nonverbal enthusiasm may be particularly relevant for this specific subgroup of children
[26]. Thus, instead of delivering interventions in a standardized way, parenting programs may benefit from an individualized approach based on insights from results of studies like the present one.

Despite the strengths and innovative aspects of ORCHIDS, there are some issues that our study is unable to take into account. Differential susceptibility to parenting may also be caused by environmental influences that alter the effects of genes (i.e., epigenetics), rather than by specific DNA sequences or a certain number of repeats alone
[48]. Human development is an active process powered by a continuous interaction between the genome and the environment

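### Ethnicity as a covariate does not protect the group × genotype test if the training effect differs by ethnicity; an ethnicity × group term would

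*Protocol article*

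**What the plan says.** The Outcomes section makes moderation the primary question: "Primary outcomes are the possible moderating effects of child genotype on the IY intervention effect". The Analyses section tests it as the interaction of group with a binary genotype in a multilevel latent growth curve model. That is the only interaction it names.

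The same section takes into account "ethnic background (i.e., Caucasian vs. non-Caucasian) and additional parental support or (mental) health care families received during the study" and then fixes how: "Ethnic background and additional care will both be used as covariates in the analyses". It mentions no product of ethnicity with group, no analysis within one ethnic group and no restriction by ancestry. Under Recruitment the exclusions are "mental retardation of the parent and/or child (IQ ≤ 70) and not mastering the Dutch language", so the sample may be ethnically mixed. Under Design, "160 will be randomly assigned to the intervention condition and 320 families to the control condition".

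**The concern.** Randomising families to training or control makes arm independent of genotype and of ethnicity. It does not make genotype independent of ethnicity. Suppose that susceptibility alleles are more common in one ethnic group and that the training works better or worse in that group, for whatever reason. Carriers and non-carriers then differ in their response to training with no genetic cause, and the group × genotype term picks this up.

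A covariate for ethnicity adjusts the outcome level. If it also predicts the growth slope, it adjusts the average rate of change. Neither adjusts the difference in training effect between ethnic groups, which is what contaminates the tested term. The contamination could produce an apparent interaction or hide a true one. The trial intends to attribute differential response to genotype and to inform the tailoring of parent training, so this attribution matters.

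**Working it through.** **No figure to reproduce.** The article gives no number on this point. Its one planning figure, N = 480 "in a two-sided test at α = .05 and power (1-β) = .80", supplies only the sample size and the nominal error rate used below.

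**Bias formula.** Let t be arm centred at its mean, G carrier status (0/1), E ethnicity (1 = non-Caucasian) and δ the difference in IY effect between the ethnic groups. The true group × genotype effect is 0. The fitted model has 1, t, G, t×G and E; the omitted term is δ·t×E. Because t is independent of G and E with mean 0, t×E is uncorrelated with 1, G and E, so it loads only on t and t×G. Hence

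bias in group × genotype = [P(E=1 | carrier) − P(E=1 | non-carrier)] × δ.

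The main effect of ethnicity does not appear in this expression, so including it changes nothing.

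**Inputs.** From the article: 160 and 320 families, two-sided 5%. Assumed, because the article gives none: 10–30% non-Caucasian families, carrier frequencies of 0.20–0.30 in Caucasian and 0.50–0.60 in non-Caucasian families, and δ of 0.2–0.4 SD. A single-outcome linear model with unit SD stands in for the slope part of the growth model.

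**Worked example** (20% non-Caucasian, carriers 0.30 vs 0.60, δ = 0.4):
- P(carrier) = 0.8 × 0.30 + 0.2 × 0.60 = 0.36
- P(E=1 | carrier) = 0.12/0.36 = 0.333
- P(E=1 | non-carrier) = 0.08/0.64 = 0.125
- bias = 0.208 × 0.4 = 0.083 SD

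**Type I error.** With overall carrier share p, SE = √[(1/160 + 1/320) × (1/p + 1/(1−p))]. For p = 0.36 this is 0.202. The error is approximately Φ(−1.96 + bias/SE) + Φ(−1.96 − bias/SE) = 7.0%. Simulation with 10,000 trials gave 6.8%.

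| Non-Caucasian | Carriers (Caucasian vs non-Caucasian) | δ (SD) | Difference in P(E=1) | Bias (SD) | Type I error, formula | Type I error, simulated |
|---|---|---|---|---|---|---|
| 10% | 0.30 vs 0.50 | 0.2 | 0.083 | 0.017 | 5.1% | not run |
| 20% | 0.30 vs 0.60 | 0.4 | 0.208 | 0.083 | 7.0% | 6.8% |
| 30% | 0.30 vs 0.60 | 0.4 | 0.265 | 0.106 | 8.3% | 8.2% |
| 25% | 0.20 vs 0.50 | 0.4 | 0.282 | 0.113 | 8.2% | not run |

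**Comparison of models.** Exact least squares was run on a grid of 10–30% non-Caucasian, carriers 0.30 vs 0.50 or 0.60, δ 0.2 or 0.4, and an ethnicity main effect of 0.5 SD. The bias (0.017 to 0.106 SD) was the same with no adjustment, with ethnicity, and with ethnicity plus ethnicity × genotype. With ethnicity × group added it was 0.000. The simulated error then fell from 6.8% to 4.8%, and from 8.2% to 5.0%.

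**When nothing is wrong.** With δ = 0, or with equal carrier frequencies (0.30 in both groups), the bias was 0 under every model.

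**The case against.** **The article may be only a summary.** It does not use the words main effect and excludes no product term. A full analysis plan could contain ethnicity × group. This stands as a limit: the point rests on the plain reading of a covariate in a section that names one interaction. The article does, however, state a form of adjustment, and that form cannot protect the primary term.

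**The inputs are invented and perhaps generous.** The article gives no ethnic mix, no carrier frequencies by ethnicity and no ethnic difference in response. A δ of 0.4 SD is twice the whole IY effect used for planning (d = .20). With 30% non-Caucasian families and an overall effect of 0.20, it implies effects of 0.08 and 0.48 (0.7 × 0.08 + 0.3 × 0.48 = 0.20), or 0.32 and −0.08. Families who do not master Dutch are excluded, which weakens language as a reason for a difference. All of this stands, so the upper end of the range should not be read as expected.

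**Stronger readings that the article does not support:**
- A reader might infer that ordinary population stratification, where ethnicity is related to genotype and to outcome level, biases the tested term. It does not: arm is randomised, so the bias is 0 even without adjustment.
- A reader might infer that the Discussion overclaims when it says experimental manipulation matters "because it is the only way to prevent confounding gene-environment covariation". That sentence concerns gene-environment covariation, which randomisation does prevent. It says nothing about confounding of genotype as a moderator.
- A reader might infer grossly inflated false positives. An error of 28.9% does appear in simulation, but only with 30% non-Caucasian families, carriers 0.30 vs 0.70 and δ = 0.8 SD, four times the planned effect.

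**Conclusion.** The point holds as a conditional weakness and an inexpensive improvement. It is not an error in a stated figure or a contradiction. The mechanism is certain: under randomisation the ethnicity covariate leaves any bias in group × genotype unchanged, and ethnicity × group removes the part carried by the recorded binary variable. The consequence is uncertain, because it needs both unequal carrier frequencies and an IY effect that varies with ethnicity or something tied to it. Under the assumed ranges the bias is about 0.02 to 0.11 SD and the type I error roughly 5% to 8%. The coding as Caucasian vs non-Caucasian cannot capture ancestry differences within the second group, so some confounding could remain after the fix.

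**What to change.** Pre-specify an ethnicity × group effect on the growth slope in every G × E model, beside the ethnicity covariate. Repeat the primary G × E test in Caucasian families only, as a sensitivity analysis. Ethnicity × genotype is optional: on its own it removed none of the bias. If the full analysis plan already contains ethnicity × group, it is enough to say so.

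The cost is one degree of freedom and a slightly wider interval for group × genotype. The standard error grows by about 1/√(1 − r²), where r is the correlation of genotype with ethnicity. In the first scenario of the table r² = (0.1 × 0.9 × 0.2)²/(0.09 × 0.32 × 0.68) = 0.017, an increase of about 1%. In the third r² = (0.3 × 0.7 × 0.3)²/(0.21 × 0.39 × 0.61) = 0.079, an increase of about 4%. The sensitivity analysis uses fewer families and will be less precise. Ethnicity is already a planned covariate, so no new data are needed, and the article reports that recruitment is still under way.
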